### Participant timeline {13}

See Fig. 2.

**Fig. 2 Fig2:**
[figure not shown]
Standard Protocol Items: Recommendations for Interventional Trials (SPIRIT) enrollment schedule, interventions, and assessments

### Sample size {14}

The power of the trial is calculated as two co-primary endpoints, sharing a combined *α*-level of 0.05. According to the literature, cumulative 30-day all-cause mortality was similar in both groups: 3.8% [8]. An equal (1:1) equivalence design was used, with *α* = 0.05 (two-sided), *β* = 0.20 (two-sided), Δ = 10%, from which the sample size *n* was estimated. In accordance with the design of the trial and the primary efficacy outcome measures, the sample size was estimated using the following formula:$$n=\frac{\pi_t\times\;\left(1-\pi_t\right)\;+\;\pi_c\;\times\;\left(1-\pi_c\right)}{\left(\mathit\triangle\mathit\;\mathit-\mathit\;\mathit{\left|{\pi_t-\pi_c}\right|}\right)^2}\times\left(\mu_{\mathit a\mathit/\mathit2}\mathit+\mu_{\mathit\beta}\right)^2$$

A minimum of 154 patients (77 per group) will need to be recruited. However, considering a potential dropout rate of 10%, combined with the low probability of adverse events in this trial, the total sample size was expanded to 170 patients.

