## Trial design {8}

The study design is a prospective, single-center, non-inferiority, randomized controlled trial. A total of 170 eligible participants will be divided randomly into two groups in a ratio of 1:1.

The flowchart of the trial is presented in Fig. 1.

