### Methods in analysis to handle protocol non-adherence and any statistical methods to handle missing data {20c}

The primary outcome will be analyzed according to the modified intent-to-treat principle, which will minimally exclude patients without receiving the assigned treatment or with missing primary outcome data. We propose declaring extracorporeal fenestration non-inferior to in situ fenestration in patients with aortic disease involving the left subclavian artery, only if shown to be non-inferior using both the “intention-to-treat” and “per-protocol” analysis sets.

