## Discussion

TEVAR for thoracic aortic pathologies involving the aortic arch provides a feasible and effective approach for such diseases and has been widely used both in the world. However, it still faces great challenges [10]. The Society for Vascular Surgery Practice Guidelines suggest routine preoperative revascularization in patients who need elective TEVAR where achievement of a proximal seal necessitates coverage of the left subclavian artery [8]. Extracorporeal fenestration and in situ fenestration techniques were initially conceived to overcome emergency or as a bail out, but in point of fact 60% or more of indications have turned out to be elective, echoing broad acceptance of the treatment and, one can suppose, its effectiveness [19, 20].

Several studies have demonstrated the safety and effectiveness of extracorporeal fenestration and in situ fenestration in patients with aortic disease involving the left subclavian artery [4–7]. However, extracorporeal fenestration or in situ fenestration techniques which is the best choice were unknown.

However, our study has several limitations. First, the surgeons cannot be blinded to the intervention. Second, the sample size is still relatively small, although we have calculated it. This was a single-center clinical trial, and multicenter clinical trials should be considered. Another limitation is that the postoperative follow-up time is short. Therefore, a worldwide large-scale clinical trial is still warranted in the future.

In summary, this study will compare the safety and validity of extracorporeal fenestration and in situ fenestration in patients with aortic disease involving the left subclavian artery. If in situ fenestration is non-inferior to extracorporeal fenestration in patients with aortic disease involving the left subclavian artery, this trial could contribute to future updates of clinical guidelines for these patients.

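### The 10-point margin is 2.6 times the assumed 3.8% mortality, so an unqualified declaration of non-inferiority would say more than the trial can exclude

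*Protocol article*

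**What the plan says.** The primary outcome is 30-day all-cause mortality (Outcomes {12}). Sample size {14} reports from the literature that "cumulative 30-day all-cause mortality was similar in both groups: 3.8" per cent, and sets Δ at 10%, alpha at "0.05 (two-sided)" and beta at "0.20 (two-sided)". It concludes: "A minimum of 154 patients (77 per group) will need to be recruited". The total is then raised to 170 for 10% dropout.

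On the decision, Methods in analysis {20c} says: "We propose declaring extracorporeal fenestration non-inferior to in situ fenestration in patients with aortic disease involving the left subclavian artery", on condition that both the intention-to-treat and the per-protocol sets show it. The margin is not repeated or qualified there. The abstract's Discussion paragraph gives demonstrating safety and validity as the aim. The closing paragraph of the main Discussion says that, given non-inferiority, "this trial could contribute to future updates of clinical guidelines for these patients". The limitations in that Discussion mention the small sample, the single center and the short follow-up, but not the margin.

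**The concern.** The endpoint is death, and the margin is larger than the whole event rate assumed in either arm. A test against such a margin rules out only a very large harm. A reader of the result will see the words non-inferior and safe, and nothing beside them will show that success leaves room for a material rise in 30-day mortality. If a technique that truly doubles early deaths has a substantial chance of earning the label, the trial's main conclusion is stronger than its evidence. The time to settle the wording is now. Once results are known, the same change would be a dispute over the main finding.

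**Working it through.** **Inputs.** From Sample size {14}: πt = πc = 0.038, Δ = 0.10, two-sided alpha 0.05 (z = 1.96), beta 0.20 labelled two-sided, 77 per group, 170 in total (85 per arm). From Methods in analysis {20c}: the declaration needs both analysis sets. My assumptions: the test is read as the upper limit of a two-sided 95% interval for the risk difference falling below 10 points, with either the Newcombe score or the Wald interval, because the article names neither.

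**Step 1: reproduce the plan's figure.** The printed formula is n = [πt(1−πt) + πc(1−πc)] / (Δ − |πt−πc|)² × (z_α/2 + z_β)².
- With beta split in two (z = 1.2816): 2 × 0.038 × 0.962 × (1.96 + 1.2816)² / 0.10² = 76.8, so 77 per arm, or 154. This is the stated figure.
- With beta not split (z = 0.8416): 57.4, so 58 per arm.

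The match at 77 confirms that Δ is an absolute difference of 10 points.

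**Step 2: size of the margin.**
- 0.10 / 0.038 = 2.63.
- Null boundary: 3.8% + 10 points = 13.8%, and 0.138 / 0.038 = 3.63.
- Expected deaths per arm: 77 × 0.038 = 2.9; 85 × 0.038 = 3.2.

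**Step 3: chance of declaring non-inferiority.** Exact enumeration of both binomial counts, control mortality 3.8%, one analysis set:

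| True extracorporeal mortality | 85 per arm, score / Wald | 77 per arm, score / Wald |
|---|---|---|
| 3.8% (equal) | 84% / 90% | 78% / 89% |
| 5.7% (1.5-fold) | 59% / 69% | 53% / 66% |
| 7.6% (2-fold) | 35% / 43% | 30% / 42% |
| 9.5% (2.5-fold) | 18% / 23% | 15% / 22% |
| 13.8% (null boundary) | 2.4% / 3.4% | 2.2% / 3.6% |

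**Step 4: what observed results pass at 85 per arm.**
- 4 deaths versus 2 (4.7% versus 2.4%, an observed doubling): upper limit 9.3 points (score) or 7.9 (Wald). Passes on both.
- 5 versus 3 (5.9% versus 3.5%): 9.9 or 8.7. Passes on both.
- 6 versus 3 (7.1% versus 3.5%): 11.4 or 10.2. Fails on both.

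**Step 5: what a margin equal to the assumed rate would need.** For illustration only, with Δ = 0.038:
- One-sided 80% power: 2 × 0.038 × 0.962 × (1.96 + 0.8416)² / 0.038² = 397.4, so 398 per arm.
- The split-beta convention behind the plan's 77: 2 × 0.038 × 0.962 × (1.96 + 1.2816)² / 0.038² = 532.0, so 533 per arm.

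**The case against.** Several points on the other side stand, and they limit how strongly this can be put.

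- **13.8% as a passing result.** A reader might infer that the trial would accept a mortality of 13.8%. It would not. That figure is the true rate at which the null hypothesis is set, and at that rate the declaration is made only 2% to 4% of the time. With 3 control deaths, at most 5 extracorporeal deaths (5.9%) pass. Error control against the stated margin is about as intended; the difficulty lies in the width of the margin and the words attached to success.
- **A doubling can never be excluded.** This is also too strong. Taking a doubling as a 3.8-point excess, and with truly equal rates, the upper limit falls below 3.8 points in 17% (score) to 27% (Wald) of trials at 85 per arm. The supportable statement is that the trial is not powered to exclude it.
- **The probabilities are upper values.** They use one analysis set. Requiring both sets to succeed can only lower them, and so would any split of alpha over the two co-primary endpoints that the sample size section mentions. Dropout is covered by the 77-per-arm column.
- **Non-inferior is always relative to a margin.** True, and nowhere does the article claim comparable mortality. The guideline sentence is hedged and follows a call for a larger trial. It also speaks of in situ being non-inferior to extracorporeal, the reverse of the declaration in {20c}, so it cannot simply be read as a use of that declaration.
- **A rationale may sit in the full protocol.** This article condenses it. The absence of a reason is therefore secondary; the size of the stated margin is visible here whatever the reason.

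None of this changes the central fact that a true doubling of deaths would often be declared non-inferior without qualification.

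**Conclusion.** The concern holds in this form: the design tests against an absolute excess of 10 points on an assumed 3.8% death rate, a 3.6-fold boundary, while the planned declaration carries no qualification and stands beside a stated aim of showing safety. A true doubling of mortality would be declared non-inferior about 35% to 43% of the time at 85 per arm and 30% to 42% at 77 per arm. These figures assume 3.8% control mortality, a two-sided 95% interval by the score or Wald method, and one analysis set. The documents do not show what smaller margin would be clinically acceptable, and none is asserted here. The 3.8-point margin in the working is only a yardstick for what 170 patients can and cannot do.

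**What to change.** Keep 170 patients and restrict the claim.

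1. In Sample size {14} and Methods in analysis {20c}, state that the margin means a true mortality of 13.8% against 3.8%, and give its clinical rationale.
2. Define success as: an excess in 30-day mortality of 10 percentage points or more is excluded. Qualify the word non-inferior with that margin wherever it is used: the abstract's Discussion paragraph, Trial design {8}, Methods for additional analyses {20b}, Methods in analysis {20c} and the main Discussion.
3. Require the risk difference with its 95% confidence interval, and the relative risk, beside every such statement.
4. State that the trial is not powered to exclude a doubling of 30-day mortality.
5. Make the guideline sentence in the Discussion conditional on that limit, and bring its direction into line with {20c}.

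The cost is protocol and analysis plan wording and a less favourable headline claim. No extra patients are needed.

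### The sample-size formula overstates power for the equivalence design it sizes (nominal 80%, exact about 57% at 77 per group); under the non-inferiority rule the 80% is roughly met

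*Protocol article*

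**What the plan says.** The section Sample size {14} takes its event rate from the literature ("cumulative 30-day all-cause mortality was similar in both groups: 3.8"%). It states that "An equal (1:1) equivalence design was used", with alpha 0.05 and beta 0.20, both called two-sided, and a margin given as "Δ = 10%, from which the sample size" is derived. The printed formula is the usual normal-approximation one, with the unpooled variance evaluated at the assumed rates. The result is "A minimum of 154 patients (77 per group) will need to be recruited". The total then becomes 170: "considering a potential dropout rate of 10%, combined with the low probability of adverse events in this trial, the total sample size was expanded to" that figure.

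Two other sections describe a different design. Trial design {8} calls the trial non-inferiority. Section {20c} gives a one-directional rule: extracorporeal fenestration is declared non-inferior to in situ fenestration "only if shown to be non-inferior using both the" intention-to-treat and per-protocol sets.

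Statistical methods {20a} names chi-square and Fisher's exact tests for categorical data. The article names no test or interval to be compared with the 10-point margin.

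**The concern.** A large-sample formula relies on the observed difference being roughly normal with a well-estimated variance. At 3.8% and 77 per group about 3 deaths per arm are expected, and the margin is 2.6 times the event rate. The approximation is poor there, so the 80% attached to 77 per group may not be the power of any test that respects the stated alpha.

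Settling the design contradiction alone would not cure this. If the same formula were used to restate power after that choice, the new figure would also be too high. With so few events, single deaths and the choice of interval can decide the result.

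**Working it through.** **Inputs, all from Sample size {14}:** mortality 0.038 in both arms (true difference 0); margin 0.10; alpha 0.05 two-sided, that is 0.025 per side; beta 0.20, called two-sided; 10% dropout; 154 minimum and 170 planned (77 and 85 per group). I take one endpoint at the full alpha.

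**Reproducing 77.** The variance term is 2 × 0.038 × 0.962 = 0.0731, and 0.0731 / 0.10² = 7.311.
- Beta split over two sides: 7.311 × (1.960 + 1.282)² = 7.311 × 10.507 = 76.8, so 77.
- Beta not split: 7.311 × (1.960 + 0.842)² = 7.311 × 7.849 = 57.4, so 58.

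Of the readings tried, only the split-beta one gives 77. That reading corresponds to 80% power for two one-sided tests, so the figure belongs to the equivalence design.

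**Power the formula implies at 77.** The standard error is √(0.0731/77) = 0.0308, and 0.10/0.0308 = 3.245. Equivalence: 2Φ(3.245 − 1.960) − 1 = 80.1%. Non-inferiority: Φ(1.285) = 90.1%.

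**Expected deaths per arm.** 77 × 0.038 = 2.9; 85 × 0.038 = 3.2.

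**Exact power.** Each pair of death counts is weighted by its binomial probability at 3.8% in both arms, and the weights are summed over the pairs that pass at 0.025 per side:

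| Rule | Per group | Formula | Score (Farrington-Manning) | Wald |
|---|---|---|---|---|
| Equivalence | 77 | 80.1% | 56.6% | 77.0% |
| Equivalence | 85 | 85.3% | 67.8% | 80.9% |
| Non-inferiority | 77 | 90.1% | 78.3% | 88.5% |
| Non-inferiority | 85 | 92.6% | 83.9% | 90.5% |

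The Newcombe interval gives the same power as the score test in all four rows. A score test calibrated to hold 2.5% along the whole null boundary gives 56.6% and 78.3% at 77, and 62% and 81% at 85. For scale, 80% exact equivalence power needs about 104 per group with the score test.

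**Exact one-sided error at 13.8% versus 3.8% (nominal 2.5%).** In the non-inferiority test, score gives 2.2% at 77 and 2.4% at 85; Wald gives 3.6% and 3.4%. In the equivalence rule, Wald gives 3.2% at both sizes. The extra Wald power is therefore bought with excess error.

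**Sensitivity to the method.** Take 4 versus 2 deaths in 77 per group. Wald z is −2.38 and passes the −1.96 criterion. Score z is −1.89 and fails, and the Newcombe upper limit is 10.2%.

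**Dropout.** 154 × 1.1 = 169.4, which explains 170. But 170 × 0.9 = 153, below 154. Dividing instead, 154 / 0.9 = 171.1, or 172 for equal arms.

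**The case against.** The strongest reply is that the protocol's declared decision rule is non-inferiority, not equivalence. Under that rule the score test at the planned 85 per group has 83.9% power with an error of 2.4%; at 77 it has 78.3% with 2.2%. This stands. A reader might infer from the 57% that the trial as a whole lacks power, or that the stated alpha and the 80% can never hold together. The documents do not support either reading, because the non-inferiority figures at 85 per group meet both.

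It is also fair that 57% combines equivalence, a score-type test and 77 rather than 85 per group, and that the article names no margin test, a choice a fuller document may make. This limits the point without removing it: at 77 per group none of the methods examined gives 80% equivalence power, and the Wald test that comes closest exceeds 2.5% per side.

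Nor does the plan claim 90% power for non-inferiority. That figure is only what the formula would give, so the gap between 90% and 78% is a warning about reusing the formula and not an error in a stated claim. Finally, large-sample formulas are common for initial sizing, and the dropout gap is one patient, worth under 1 point of power. Both are true.

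**Conclusion.** The concern holds in a limited form. For the equivalence design named in the sample-size section, the nominal 80% at 77 per group is wrong as stated: exact power is about 57%, and about 68% at 85, with a score test. Wald reaches about 77% and 81% only with a one-sided error of about 3.2 to 3.6%. Under the non-inferiority rule, power is about 78% and 84% in a single analysis set, so the 80% is roughly met.

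These figures assume true mortality of 3.8% in both arms and 0.025 per side. Requiring success in both analysis sets lowers power further, by an amount the documents do not fix. As an illustration, with 85 per arm complete for intention-to-treat and an assumed 10% excluded at random from per-protocol, simulation gave about 75 to 76% with the score test; with no exclusions it stays at 83.9%.

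The dropout slip is minor. The step to 170 is already used up by the 10% inflation, so it contains no separate allowance for a low event probability.

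**What to change.** Keep 170 patients and change the wording.

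1. Reconcile the equivalence design in Sample size {14} with the non-inferiority design in {8} and {20c}.
2. State that the 10-point margin is tested with a two-sided 95% score interval (Miettinen-Nurminen or Farrington-Manning) for the 30-day risk difference.
3. Replace the formula-based power with exact power for that rule: for non-inferiority about 78% at 77 and 84% at 85 per group; if equivalence is kept, about 57% and 68%. Add that requiring both analysis sets reduces this, and give the per-protocol exclusions assumed.
4. Correct the dropout sentence to say that 170 less 10% leaves 153 evaluable, and drop the statement that 170 also allows for the low event probability.

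No extra patients or procedures are needed. The cost is a less favourable stated power, markedly so if equivalence is retained.

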### Outcomes {12}

In this trial, the outcomes will be developed according to the standard clinical endpoint of endovascular aortic repair [17]. The primary outcome will be the all-cause mortality (30 days). The secondary outcomes will include incidence of secondary intervention (30 days, 6 months, 1 year), incidence of endoleak (30 days, 6 months, 1 year), incidence of major adverse events (MAE) (i.e., immediate procedural success and complications) (30 days, 6 months, 1 year), immediate technical success rate, and all-cause mortality (6 months, 1 year). All-cause mortality is the annual number of deaths in a given group per the population in that group. Endoleak was assessed by DSA angiography during surgery and by CTA and DUS after surgery. We recommend re-intervening to achieve a proper seal in patients with type I or type III endoleaks following TEVAR according 2024 ESC Guidelines [18]. We recommend to perform 30-day imaging after TEVAR, by CTA and DUS, to assess the success of intervention. A secondary intervention will be performed if necessary, based on the follow-up results and the patient’s condition.

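### The sample-size section sizes an equivalence trial with two co-primary endpoints, but the protocol declares a non-inferiority trial with one primary outcome, so the stated power, hypothesis and alpha do not belong to the planned test

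*Protocol article*

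**What the plan says.** All quotes are from the Protocol article.

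- **Sample size {14}, design and error rates:** "An equal (1:1) equivalence design was used, with *α* = 0.05 (two-sided), *β* = 0.20 (two-sided), Δ = 10" per cent. The printed formula multiplies the variance term by the square of u for alpha/2 plus u for beta; the beta subscript is not halved.
- **Sample size {14}, event rate:** "cumulative 30-day all-cause mortality was similar in both groups: 3.8% [8".
- **Sample size {14}, endpoints:** "The power of the trial is calculated as two co-primary endpoints, sharing a combined" alpha level of 0.05.
- **Sample size {14}, result:** "A minimum of 154 patients (77 per group) will need to be recruited". The total is then raised to 170, "considering a potential dropout rate of 10" per cent and the low event probability.
- **Trial design {8}:** "The study design is a prospective, single-center, non-inferiority, randomized controlled trial".
- **Outcomes {12}:** "The primary outcome will be the all-cause mortality (30 days"). Every other outcome there, and in the abstract, is listed as secondary.
- **Sections {20b} and {20c}:** non-inferiority is to be tested in the intention-to-treat and per-protocol sets, and declared only if both show it. No equivalence conclusion is planned anywhere.

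**The concern.** A sample-size section should fix three things for the primary analysis: the hypothesis, the significance level and the power. Here each disagrees with another part of the protocol. The hypothesis is equivalence in one section and non-inferiority in the others. The significance level is either the whole 0.05 or a share of it. The power is stated through a beta of 0.20 that belongs to the two-sided equivalence question. The printed formula, read literally, does not return the printed number either.

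At stake is which test, at which level, will decide the trial. If that stays open until the data are seen, the hypothesis and the level can be chosen afterwards. Readers would also be given a power figure for a conclusion that the trial does not intend to draw.

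**Working it through.** **Inputs** (all from Sample size {14}): mortality 3.8% in both arms, so the assumed difference is 0; margin 10 percentage points; alpha 0.05 two-sided, quantile 1.960; beta 0.20, labelled two-sided; 1:1 allocation.

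**Common factor.** [0.038 × 0.962 + 0.038 × 0.962] / 0.10² = 0.073112 / 0.01 = 7.3112.

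**1. Reproducing the plan's figure.** Halve the two-sided beta to 0.10, as in an equivalence calculation (quantile 1.282):
7.3112 × (1.960 + 1.282)² = 76.8, so 77 per group and 154 in total. This matches exactly.

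**2. The formula as printed.** Use the beta term unhalved at 0.20 (quantile 0.842):
7.3112 × (1.960 + 0.842)² = 57.4, so 58 per group and 116 in total. This does not match.

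**3. Power at 77 per group for each hypothesis.** The standard error is √(0.073112 / 77) = 0.03081, and 0.10 / 0.03081 − 1.960 = 1.285.
- Non-inferiority: Φ(1.285) = 0.901.
- Equivalence: 2 × 0.901 − 1 = 0.801.

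So the stated 80% is the equivalence power. The formula power for the declared non-inferiority question is about 90%.

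**4. Was alpha shared?** An equal split gives each endpoint 0.025 two-sided (quantile 2.241):
- unhalved beta: 7.3112 × (2.241 + 0.842)² = 69.5, so 70 per group;
- halved beta: 7.3112 × (2.241 + 1.282)² = 90.7, so 91 per group.

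Neither is 77. The calculation spends the full 0.05 on one endpoint.

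**5. How far the normal formula can be trusted.** Expected deaths are 77 × 0.038 = 2.9 per arm, or 85 × 0.038 = 3.2. Enumerating the binomial outcomes at 3.8% in each arm, with one-sided alpha 0.025 and the 10-point margin, gives this non-inferiority power:

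| Per group | Formula | Score test | Wald interval |
|---|---|---|---|
| 77 | 90.1% | 78.3% | 88.5% |
| 85 | 92.6% | 83.9% | 90.5% |

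The score test and the Wald interval are illustrations; the protocol names neither for this comparison.

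**6. Dropout.** 170 × 0.90 = 153, one below the stated minimum of 154. Dividing instead gives 154 / 0.90 = 171.1, or 172 for equal arms. The 170 corresponds to 154 × 1.1 = 169.4.

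**The case against.** The strongest reply is that the number is sound. The section states an equivalence design and labels beta as two-sided, and with those inputs 77 follows exactly. A reader who applies the printed formula might infer that the true requirement is 58 and that 77 is a miscalculation. The documents do not support that: the mismatch lies in the printed beta subscript. Nor is the halved beta the only route to 77. Non-inferiority at 90% power gives the same number, and a continuity correction applied to 57.4 gives 76.1, which also rounds up to 77, although the text mentions no such correction.

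The second reply is that sizing for equivalence is conservative when only non-inferiority is claimed, so nobody is harmed. By the formula this is right, and at the planned 85 per group both illustrative tests exceed 80%. A reader might infer from the exact figures that the trial is underpowered; at full enrolment this is not shown, and the figures rest on tests that the protocol does not specify. The opposite inference, that the trial is simply oversized, is not safe either, because the score test falls just under 80% at 77 per group.

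The third reply is that the dropout shortfall is one patient. That is fair, and it is minor.

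What none of this answers is the conflict of design labels, the power attached to the wrong hypothesis, and a second primary endpoint that is defined nowhere.

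**Conclusion.** The point stands as a contradiction in the basis of the sample size, not as a wrong sample size.

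- The beta term in the printed formula does not match the value used: 58 against 77 per group.
- The section powers equivalence while the protocol tests non-inferiority: 80% stated, against about 90% by the formula for the declared question.
- The sentence on co-primary endpoints has no counterpart in the outcomes and no effect on the calculation. Taken literally with an equal split, it would halve the significance level for the primary test.

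These figures assume 3.8% mortality in both arms, the 10-point margin and, for the formula power, a normal approximation that is weak at about three deaths per arm. The correction is needed before analysis because it settles the hypothesis and alpha of the primary test.

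**What to change.** Keep 170 patients and rewrite Sample size {14}:

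1. Delete the sentence on two co-primary endpoints and shared alpha. Name 30-day all-cause mortality as the single primary endpoint.
2. Replace equivalence with non-inferiority, tested at one-sided 0.025, which corresponds to one bound of a two-sided 95% interval and uses the same 1.960. State the direction as well: section {20c} asks whether extracorporeal is non-inferior to in situ fenestration, while the last paragraph of the Discussion puts it the other way round.
3. Make the beta term match the value used: beta = 0.10, u = 1.282, with the two-sided label removed. Give the formula power as about 90% at 77 per group.
4. Add that, with about three deaths expected per arm, the exact power depends on the test chosen: for example about 78% (score) or 89% (Wald) at 77 per group, and 84% or 90% at 85.
5. Minor: state that 10% dropout from 170 leaves 153 evaluable patients.

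The cost is a revised paragraph and one short power calculation, with no additional patients. If the sponsor did intend equivalence, the design, decision-rule and analysis sections would have to change instead, and the co-primary sentence would still have to go unless a second primary endpoint is defined.
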